## Methods

The RESearch on the PrEvalence and the diagnosis of COPD and its Tobacco-related etiology (RESPECT) study is a collaboration between Université Catholique de Louvain (Belgium), the North-West State Medical University (named after I.I. Mechnikov, St. Petersburg) and the Northern State Medical University, Arkhangelsk (RF).

### Setting

Two northwestern RF cities (St. Petersburg and Arkhangelsk) were selected for the RESPECT study. The population sizes of St. Petersburg and Arkhangelsk have been estimated as 4,869,600 citizens (1st January, 2011) [29] and 356,500 citizens (1^st^ January, 2010), respectively [30].

Fifteen primary care centers were invited to participate in this study. These centers are located in different areas of these cities (some in highly polluted areas, others in less polluted areas) and were selected to provide adequate coverage of the different districts.

Fifteen investigators (10 from St. Petersburg and 5 from Arkhangelsk) were recruited (predominantly doctors and two highly educated nurses). All investigators received study information, including a detailed study protocol and recent guidelines on COPD, and participated in a three-week course on spirometry and the clinical diagnosis and management of obstructive lung diseases.

### Design

This study includes three components: a cross-sectional study (prevalence and diagnostic), a case-control study and a cohort study (Fig. 1).

**Fig. 1 Fig1:**
[figure not shown]
Design of the RESPECT study. A = Arkhangelsk, StP = Saint Petersburg, Q = questionnaire, IPCRG = International Primary Care Respiratory Group, V = visit, S = Study (S1 – cross-sectional, S2 – case-control, S3 – cohort), GOLD = Global Initiative for Chronic Obstructive Lung Disease, COPD = Chronic Obstructive Lung Disease. FEV_1_ – forced expiratory volume in 1 s, FEV_1_/FVC = forced expiratory volume in 1 s/forced vital capacity ratio, LLN = lower limit of normal

### Study I (prevalence and diagnosis)

#### Sample size calculations

The sample size was calculated based on two goals: 1) to determine a reliable estimate of the prevalence of COPD and 2) to estimate the diagnostic value of symptoms with an acceptable confidence interval.

To generate a reliable estimate of the prevalence of COPD, for which 8 % prevalence in the RF was assumed, the following formula was used: $$ n=\frac{Z^2P\left(1-P\right)}{d^2} $$, where n is the sample size, Z is the Z statistic for a level of confidence (95 %), P is the expected prevalence (8 %), and d is the desired precision (1 %) [31]. Therefore, based on our prevalence considerations, the sample size for the RESPECT study was estimated using 2828 subjects.

To estimate the diagnostic value of various signs and symptoms with an acceptable confidence interval (the second focus of our cross-sectional study), sample size considerations were based on the following premises: 1) the expected prevalence of important symptoms (i.e., chronic cough, dyspnea, wheezing, chronic phlegm) of COPD in the general population was 10 %; 2) a worst-case scenario that none of these criteria displayed any diagnostic value (i.e., the proportion of each symptom would be 0.5 in each group) given an acceptable confidence interval of 95 %; and 3) based on an 8 % prevalence of COPD. Based on these premises, a sample size of 864 was established.

Based on both of these approaches and assuming an anticipated refusal rate of 20 %, 3500 participants from St. Petersburg and 1500 from Arkhangelsk were invited to participate in this study.

In order to estimate the sample size needed for the case-control study the following formula was used $$ n=\left(\frac{r+1}{r}\right)\frac{\sigma^2{\left({Z}_{\beta }+{\mathrm{Z}}_{\alpha /2}\right)}^2}{{\left(d\mathrm{ifference}\right)}^2} $$ ; r stands for the ratio cases/controls (we choose for an equal number of cases and controls), *Z*_*β*_ = the desired power (for 80 % power *Z*_*β*_ = .84) , Z_*α*/2_ = the desired level of significance (for 0.05 significance level, Z_*α*/2_ =1.96), *σ*^2^ = the variance of the outcome variable (for Log hCRP = 0.25 ) and *d =* the difference in means that is considered meaningful (for log hCRP we used 0.4 as the minimum meaningful difference). The number of cases and controls needed was estimated in this way as 63. Taking into account a potential drop out of 10 % it was decided to involve 70 heavy smokers with established airflow limitation and 70 heavy smokers with normal lung function.

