## Background

Chronic obstructive pulmonary disease (COPD) remains a major public health problem in the 21st century. COPD is one of the leading causes of morbidity and mortality worldwide and results in an economic and social burden that is both substantial and increasing [1].

In the Russian Federation (RF), COPD represents more than 55 % of all pathologies of the respiratory system [2]. At present, approximately 2 million cases of COPD have been reported in the RF, but the actual number is estimated to be approximately 11 million [3, 4]. Several attempts to estimate the prevalence of COPD in different regions of the RF have been undertaken. These studies revealed significant differences in the prevalence of COPD based on sex, age, ecological conditions, socioeconomic status, and smoking habits, resulting in prevalence rates ranging from 1.8 to 32.0 % [5, 6]. Therefore, there is a consensus that the prevalence of COPD in the RF is underestimated and that additional reliable data are needed.

Smoking is a major risk factor for COPD, and this behavior is highly prevalent in the RF. A total of 39.1 % of all Russians (43.9 million) are current smokers (60.7 % of males and 21.7 % of females) [7]. Higher-educated Russians (vocational secondary: 41.3 %, higher education: 38.1 %) are more frequent smokers than less-educated Russians (primary: 18.0 %). Smoking is also more prevalent among urban populations (40.2 %) compared with rural populations (35.9 %).

Occupational hazards and both outdoor and indoor pollutants are also important risk factors for COPD [8–11].

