#### Population

The study population was randomly selected from the lists of the 15 participating centers (these patient lists are organized based on territories).

This study focused on the early stages of COPD; therefore, participants aged 35–70 years were selected from each center using a random number generator and were subsequently invited to participate.

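### The ±1-point prevalence precision behind n = 2828 assumes a simple random sample, but participants came from the lists of 15 selected centres and no design effect is allowed for

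*Protocol article*

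**What the plan says.** Sample size calculations gives n = Z²P(1−P)/d² with P = 8%, d = 1% and 95% confidence, and states that "the sample size for the RESPECT study was estimated using 2828 subjects". The only inflation named there is for refusal: "assuming an anticipated refusal rate of 20 %, 3500 participants from St. Petersburg and 1500 from Arkhangelsk were invited".

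Population describes the draw: "The study population was randomly selected from the lists of the 15 participating centers", and adds that these lists are organised by territory. Setting says that the centres were invited and selected to cover the different districts, "some in highly polluted areas, others in less polluted areas". No random draw of centres is described. Setting also reports: "Fifteen investigators (10 from St. Petersburg and 5 from Arkhangelsk) were recruited".

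The first objective, at the end of Background, is the prevalence among adults aged 35–70 in St. Petersburg and Arkhangelsk, by environmental conditions and socioeconomic status among other factors. The target is therefore the two cities, not the 15 lists.

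Statistical analysis names the software and bivariate and multivariate analyses. It does not mention centre, operator or a variance method.

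**The concern.** The formula holds when individuals are sampled independently from the target population. Here people share a centre, a territory and possibly an operator. If true prevalence or its measurement differs between centres, people from one centre carry partly the same information, and the variance of the overall estimate grows with the number per centre. At about 198 per centre, even a very small ICC matters.

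Two things are at stake. The stated planning precision for the first objective is too favourable. And any interval or test that ignores centre would overstate certainty. Comparisons by pollution level are the most exposed: the lists are territorial and the centres lie in areas of differing pollution, so this exposure varies largely between centres and the information is nearer to 15 units than to 3000. The exposure questionnaire also records years lived in a polluted area for each person, so it is not purely a centre-level variable.

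**Working it through.** **Inputs.** P = 0.08, d = 0.01, Z = 1.96, 20% refusal and 5000 planned invitations (Sample size calculations); 15 centres (Setting, Population); 4419 invited, 3133 enrolled, 2974 with acceptable spirometry (Results). The ICC is assumed.

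**1. The article's own figure.** 1.96² × 0.08 × 0.92 / 0.01² = 3.8416 × 0.0736 / 0.0001 = 2827.4, rounded up to 2828. It reproduces with a design effect of exactly 1.

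**2. Precision as achieved, without clustering.** At n = 2974: 1.96 × √(0.0736/2974) = 0.98 points. There is almost no slack.

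**3. Precision with clustering.** Average number per centre m = 2974/15 = 198.3. Design effect (DEFF) = 1 + (m − 1) × ICC. Half-width = 1.96 × √(0.0736 × DEFF/2974). For t on 13 df (15 centres minus 2 city strata), multiply by 2.160/1.96 = 1.10. Between-centre SD = √(ICC × 0.0736). Coverage of an unadjusted 95% interval = 2Φ(1.96/√DEFF) − 1.

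| Assumed ICC | Between-centre SD (points) | DEFF | Effective n | Half-width, z | Half-width, t on 13 df | Coverage if unadjusted |
|---|---|---|---|---|---|---|
| 0.002 | 1.2 | 1.39 | 2133 | ±1.15 | ±1.27 | 90% |
| 0.005 | 1.9 | 1.99 | 1497 | ±1.37 | ±1.51 | 84% |
| 0.01 | 2.7 | 2.97 | 1000 | ±1.68 | ±1.85 | 74% |
| 0.02 | 3.8 | 4.95 | 601 | ±2.17 | ±2.39 | 62% |

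The formula takes centres as equal in size.

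**4. Where ±1 point is lost.** Setting n/DEFF = 2827.4 gives ICC = (n/2827.4 − 1)/(n/15 − 1). At n = 2974 this is 0.0519/197.3 = 0.0003, a between-centre SD of about 0.4 points around 8%. At all 3133 enrolled it is 0.1081/207.9 = 0.0005.

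**5. Could more subjects cure it?** With 15 centres the effective n cannot exceed 15/ICC however many are recruited. Once the ICC exceeds 15/2828 = 0.0053, ±1 point cannot be reached at any sample size.

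**6. Did the planned surplus cover it?** Refusal alone needs 2828/0.8 = 3535 invitations. The 5000 planned would yield 5000 × 0.8 = 4000, room for a DEFF of 4000/2827.4 = 1.41, that is an ICC of 0.4147/265.7 = 0.0016. Only 4419 were invited and 3133 enrolled.

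**The case against.** **Centres as strata.** If the 15 lists are treated as fixed strata, random selection within each gives a sampling design effect near or below 1. That would be right if those lists were the whole target, but the stated target is the adult population of two cities. It does stand that centres which were not randomly drawn do not by themselves justify a design-based variance on 13 df. Treating centre as a cluster is a defensible working model, not the only one.

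**No ICC is given.** True, so the size of the loss is assumed throughout. Background does say that earlier Russian studies found marked differences, "resulting in prevalence rates ranging from 1.8 to 32.0" per cent, but these come from different regions and populations and do not measure variation between centres within a city. The relevant ICC is within city and may lie at the low end of the range.

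**Surplus invitations and non-response analysis.** The surplus is real, but the article does not attribute it to clustering and recruitment did not reach it. The Sensitivity analysis section addresses non-participation, not clustering.

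**Stronger readings that the article does not support.**
- A reader might infer that the published intervals will be too narrow. Statistical analysis fixes no variance method and the full analysis plan is not shown, so this holds only if centre is ignored.
- Fifteen investigators and 15 centres might suggest one operator per centre, with operator and centre effects inseparable. That is possible but not stated, and the article describes common spirometry training, quality feedback and grading of every spirogram.
- A reader might take the centres as chosen to contrast pollution levels. The stated reason is coverage of districts.
- A reader might extend the point to the comparison of GOLD with LLN prevalence. Both criteria are applied to the same spirograms, so centre effects common to both largely cancel in the difference, and the ICC of a single prevalence does not carry over.

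**Conclusion.** The arithmetic of 2828 is correct; its sampling assumption does not match the design described. With any appreciable variation between centres the ±1 point is not delivered. At n = 2974 the half-width runs from about ±1.15 to ±2.17 points for assumed ICCs of 0.002 to 0.02. The direction holds for any positive ICC; the size rests on the assumed ICC, roughly equal centre sizes and inference to the two cities.

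The consequence for reported intervals is conditional on the analysis method. Clustering widens intervals; it does not by itself bias the prevalence estimate. Recruitment is complete, so the remedy lies in the stated precision and the analysis, not in the number of subjects.

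**What to change.** - Replace the single ±1-point figure with a range of half-widths over assumed ICCs, labelled as assumptions.
- Compute prevalence intervals with city as stratum and centre as cluster, using a t reference with about 13 df. Say that centres were selected rather than randomly drawn.
- In the multivariable models, allow for centre by a random effect or by cluster-robust errors with a small-sample correction. This matters most for pollution.
- Report the observed ICC and the number of participants per centre. State how investigators were assigned to centres, so that readers can judge whether operator and centre effects can be separated.

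Cost: analysis wording and a survey or mixed-model procedure, with no new subjects. The downside is wider intervals and a less favourable stated precision.

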### Study II (case-control study)

#### Study population and sample size

One hundred patients with COPD and a smoking history of more than 10 pack-years (cases) and one hundred patients with the same smoking history without COPD (controls) will be invited in the second study in order to reach the needed sample size of 2 × 70 patients.

The inclusion criteria for the cases and the controls include the following: 1) a smoking history of more than 10 pack-years and 2) age between 35 and 70 years.

The cases and the controls will be matched based on the following criteria: age group, sex, smoking history, level of pollution in living area, body mass index, comorbidity (cardio-vascular diseases index, systemic disease, and tuberculosis in anamnesis), and use of medications that may influence the inflammatory status.

The cases will include 100 participants that meet the following criteria: 1) smokers aged 35–70 years with a smoking history of >10 pack-years; 2) completely irreversible AL based on the following criteria: FEV_1_/FVC < 0.7 according to the GOLD criteria (fixed threshold) or FEV_1_/FVC < LLN; 3) COPD of stage II-IV according to the GOLD criteria (post-bronchodilation FEV_1_ < 80 % of the predicted value) or the LLN criteria (FEV_1_ below the LLN); and 4) a confirmed diagnosis of COPD by a pulmonologist after a comprehensive clinical examination.

The controls will include 100 participants based on the following criteria: 1) smokers aged 35–70 years with a smoking history of >10 pack-years and without COPD according to the GOLD or LLN criteria, 2) without asthma (absence of symptoms), 3) no history of allergies, and 4) free from the use of bronchodilators.

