## Results

Participants aged 35-70 years from the patient list from each center were selected using a random number generator; initially, 4419 individuals were invited to participate in the study. In total, 3133 individuals agreed to participate and met the inclusion criteria. In addition, 2974 participants demonstrated satisfactory quality on spirometry (after comprehensive quality assessment for reproducibility and acceptability) (Fig. 2). Basic spirometry analysis revealed 247 participants with obstructions before bronchodilation (FEV_1_/FVC < 0.7). Good-quality bronchodilator tests were obtained from 2388 participants. Of these participants, 162 were patients with AL (FEV_1_/FVC < 0.7), including 130 patients with irreversible lung obstruction (FEV_1_ < 200 ml or 12 % after bronchodilation).

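### The case-control sample size of 63 per group does not follow from its printed formula and inputs, which give 25 per group

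*Protocol article*

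**What the plan says.** The calculation is in the Protocol article, Methods, Study I, Sample size calculations, in the paragraph on the case-control study. It prints the usual formula for comparing two means and assigns a value to every term:

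- Allocation: "we choose for an equal number of cases and controls", so r = 1.
- Power 80 %, with a Z value of 0.84.
- Two-sided error rate: 1.96 is used "for 0.05 significance level".
- Variance: "for Log hCRP = 0.25".
- Difference: "for log hCRP we used 0.4 as the minimum meaningful difference".

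The result is then given: "The number of cases and controls needed was estimated in this way as 63". A 10 % drop-out allowance raises this to 70 smokers with airflow limitation and 70 with normal lung function. Study II, Study population and sample size, carries the target forward: 100 cases and 100 controls are to be invited "in order to reach the needed sample size of 2 × 70 patients".

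**The concern.** The article presents 63 as the output of this formula with these inputs. All the inputs are printed, so the claim can be checked directly, and it fails by a wide margin. The figure of 63 leads to the target of 70 per group and the 100 invitations per group. As printed, a reader cannot tell which difference in log hCRP Study II has 80 % power to detect, or how much of the planned recruitment the stated aim requires. Study II is described as still to come, so a correction is still useful.

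**Working it through.** **Formula as printed.** n per group = ((r+1)/r) × σ² × (Zβ + Zα/2)² / difference².

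**Inputs, all from the same paragraph.** r = 1, so (r+1)/r = 2; Zβ = 0.84; Zα/2 = 1.96; σ² = 0.25 (SD 0.5); difference = 0.4.

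**Attempt to reproduce 63.**

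- (0.84 + 1.96)² = 2.80² = 7.84
- 2 × 0.25 × 7.84 = 3.92
- 3.92 / 0.4² = 3.92 / 0.16 = 24.5, so 25 per group and 50 in total
- With 10 % drop-out: 25 / 0.9 = 27.8, so 28 per group

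The stated 63 is not reproduced. The ratio is 63/25 = 2.5.

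**The drop-out step is correct.** 63 / 0.9 = 70. This also shows that 63 is meant per group, since it becomes 70 and 70. Read as a total it would still be wrong, because the inputs give 50.

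**Other readings tried, with the printed variance and difference unless noted.**

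| Variant | n per group |
|---|---|
| One-sided 0.05 | 20 |
| t-test instead of normal approximation | 26 |
| 0.25 read as an SD | 7 |
| SD 0.5 used where the variance belongs | 49 |
| Difference not squared | 10 |
| Power 90 % | 33 |
| Power 95 % | 41 |
| Power 99 % | 58 |
| Alpha 0.01 | 37 |
| Alpha 0.001 | 54 |
| Rank-test inflation | about 26 to 29 |

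None gives 63. A ratio of r = 0.25 comes close (61.25, so 62), but the stated equal groups rule it out.

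**What 63 per group would deliver with the printed inputs.** The standard error of the difference is √(2 × 0.25/63) = 0.0891. Power = Φ(0.4/0.0891 − 1.96) = Φ(2.53) = 0.994. At 25 per group the same calculation gives 80.7 %, and at 70 per group 99.7 %.

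**What inputs would give 63.** In standardised form n = 2 × 7.84 / δ², where δ = difference/SD. For δ = 0.5, n = 15.68 / 0.25 = 62.72, so 63. The printed inputs imply δ = 0.4/0.5 = 0.8. Two examples with δ = 0.5:

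- difference 0.25, variance 0.25: 2 × 0.25 × 7.84 / 0.0625 = 62.72
- difference 0.4, variance 0.64: 2 × 0.64 × 7.84 / 0.16 = 62.72

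These are examples only. Any pair with a standardised difference of 0.5 gives the same n.

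**Detectable difference at 63 completers per group, variance 0.25, 80 % power.** 2.80 × 0.0891 = 0.249, so about 0.25.

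**The case against.** The strongest reply is that the slip does no harm at the planned size. If the printed variance and difference are right, 63 completers per group give far more than 80 % power. If an input was misprinted and the intended standardised difference was 0.5, then 63 gives the claimed 80 %. On either account the planned number meets or exceeds the stated power. The error is also confined to the case-control component and does not touch the prevalence calculation. This stands, and it limits the point: what is shown is a wrong or unsupported figure, not an underpowered study. It does not remove the point, because the article ties 63 to inputs that do not produce it and no other section repairs the mismatch.

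Two stronger readings are tempting, but the article does not support them.

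- A reader might infer that Study II cannot find enough cases, because Results counts 162 with airflow limitation, "including 130 patients with irreversible lung obstruction", before the smoking, severity and pulmonologist-confirmation criteria are applied. That count covers only the fixed 0.7 ratio among the 2388 participants with good-quality bronchodilator tests, whereas Study II also admits cases defined by the lower limit of normal. The article gives no smoking breakdown of the obstructed participants and does not say that cases must come from this count. The 28 % never-smoker share in the Discussion comes from an external study of people aged 40 to 98. Even applied here it leaves 130 × 0.72 = 93.6, about 94, before the remaining criteria, whose effect cannot be quantified from the article.
- A reader might infer that one particular input, such as the difference, was misprinted. The arithmetic cannot identify which element is wrong.

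**Conclusion.** The point holds as a contradiction between a stated sample size and its own formula. The printed inputs give 24.5, so 25 per group (28 with 10 % drop-out), against a stated 63 (70 with drop-out). The 80 % power claim does not match 63 per group under those inputs, where power is about 99.4 %. The conclusion rests only on values printed in the paragraph and on reading 63 as per group, which the step to 70 and 70 confirms. The article does not show whether the sample size, the variance or the difference is wrong, and it shows no loss of power at the planned size.

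**What to change.** Check the source calculation and restate one consistent set of variance, difference, power and n in the case-control paragraph of Sample size calculations. If the printed variance and difference are correct, the required number at 80 % power is 25 per group, or 28 with drop-out. If 63 is correct, print the variance and difference that produced it. If the target of 2 × 70 in Study II is kept in either case, state what it provides: the power for the chosen difference, or the difference detectable with 80 % power. The latter is about 0.25 on log hCRP at 63 completers per group if the variance is 0.25. The cost is one corrected paragraph and no new patients.

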#### Population

The study population was randomly selected from the lists of the 15 participating centers (these patient lists are organized based on territories).

This study focused on the early stages of COPD; therefore, participants aged 35–70 years were selected from each center using a random number generator and were subsequently invited to participate.

